## Abstract

**Background:**

Adolescents and young adults (AYAs) with cancer are at risk of poor psychosocial outcomes. AYAs grew up with the internet and digital technology, and mobile Health (mHealth) psychosocial interventions have the potential to overcome care access barriers.

**Objective:**

This pilot randomized controlled trial (RCT) aimed to establish the feasibility, acceptability, and preliminary efficacy of a fully automated mobile app version of the Promoting Resilience in Stress Management intervention (mPRISM). Promoting Resilience in Stress Management is an evidence-based intervention developed in collaboration with AYAs, based on stress and coping theory, resilience theory, and evidence-based coping strategies. We hypothesized that mPRISM would be feasible, acceptable, and appropriate.

**Methods:**

This is a parallel, 2-arm, single-site pilot RCT with a waitlist control design. The study will recruit 80 AYAs with cancer from a clinic. Eligible AYAs are aged 12 to 25 years, within 12 months of a new cancer diagnosis, receiving chemotherapy or radiation therapy, speak, read, or write in English, and are cognitively able to participate in study procedures. Recruitment by clinical research coordinators will occur remotely by phone, video, or text. Participants will be randomized to psychosocial usual care (UC) alone or UC plus mPRISM for an 8-week intervention period, and will remain unblinded to study condition. Enrolled participants will complete surveys at baseline before randomization, 8 weeks, and 3-month follow-up. Using a waitlist design, the UC arm will receive mPRISM upon completion of 3-month follow-up surveys. Those in the UC arm will complete 2 additional measurement points at immediate posttreatment and 3 months later. The primary outcomes of interest are feasibility, defined as ≥60% enrollment and ≥70% retention (ie, percentage of participants who completed the study), and “feasibility, acceptability, and appropriateness” as defined by cut-off scores ≥4/5 on 3 brief validated implementation outcome measures (feasibility of implementation measure, acceptability of intervention measure [AIM], intervention appropriateness measure [IAM]). We will apply top-box scoring for the implementation measures. Exploratory outcomes of interest include patient-reported health-related quality of life, resilience, distress, anxiety, depression, pain, and sleep. We will conduct an intention-to-treat analysis to compare the outcomes of the mPRISM arm versus the control arm with covariate-adjusted regression models. We will summarize individual digital usage metrics using descriptive statistics.

**Results:**

Since September 2023, we have enrolled 20 participants and recruitment is ongoing.

**Conclusions:**

Although our previous work suggests AYAs with cancer are interested in mHealth psychosocial interventions, such interventions have not yet been sufficiently evaluated or implemented among AYA oncology patients. mPRISM may serve as a potential mHealth intervention to fill this gap. In this study, we will test the feasibility, acceptability, and preliminary efficacy of mPRISM. This work will inform future larger-scale RCTs powered for efficacy outcomes.

**Trial Registration:**

ClinicalTrials.gov NCT05842902; https://clinicaltrials.gov/study/NCT05842902

**International Registered Report Identifier (IRRID):**

DERR1-10.2196/57950

## Introduction

Pediatric adolescents and young adults (AYAs), 12-25 years old, with cancer experience unique developmental and psychosocial needs because cancer disrupts typical developmental experiences and life transitions including the pursuit of educational and vocational goals and the establishment of social, personal, and sexual identity [1]. AYAs with cancer experience poor psychosocial outcomes including social isolation, behavioral adjustment problems, depression, anxiety, and stress [2,3]. In addition, quality of life (QoL) and psychosocial outcomes among AYA cancer survivors are inferior to their younger pediatric and older adult counterparts [4]. Such sequelae are further associated with negative long-term survivorship outcomes such as low educational attainment, unemployment, and financial dependence [5]. Elevated psychological distress in AYA cancer survivors is associated with medical costs of US $4415 per year [6].

The Promoting Resilience in Stress Management (PRISM) program is an evidence-based resilience intervention designed for and in collaboration with AYAs [7-13]. PRISM is a brief, manualized, evidence-based intervention delivered one-to-one in person by layperson coaches. PRISM was developed based on iterative research within the AYA and pediatric oncology population, stress and coping theory, resilience theory, and evidence-based cognitive-behavioral and mindfulness interventions [7-13]. Previous studies suggest in-person delivery of PRISM is feasible and valuable to AYA patients and parents [11,12]. In a randomized controlled trial (RCT) of AYAs with cancer, PRISM was associated with improved self-reported resilience, distress, and health-related quality of life (HRQoL), with moderate effect sizes [14,15]. However, despite these promising effects, major barriers limit the dissemination and reach of in-person interventions such as PRISM, including geographic proximity, transportation, limited trained personnel, and treatment costs.

Skills-based psychosocial interventions are increasingly deployed through mobile Health (mHealth) platforms [16,17] and show promise in early research in youth with chronic illnesses [18]. Smartphones have become ubiquitous [19], irrespective of gender, race and ethnicity, and socioeconomic status [20]. The implementation of mHealth-based care delivery has the potential to improve access to evidence-based treatment and reduce health disparities; for example, 73% of families living below the poverty line in the United States have one or more smartphones and digital interventions have been proposed as a feasible means of disseminating health programs in homeless populations [21,22]. Thus, mHealth interventions have the potential to be universally accessible regardless of geographic, financial, and infrastructure constraints. mHealth platforms confer the advantages of appeal (self-pacing, instant availability, anonymity), reach, and cost-effectiveness [23-25]. This may be particularly important for meeting the needs of AYAs, who grew up in the digital age and are accustomed to interacting on smartphones and prefer internet-based self-help [24,26]. Smartphone adoption and internet use have skyrocketed among younger generations, with 95%-96% of teenagers and young adults in the United States owning a smartphone [27,28]. The internet serves as a primary means of physical- and mental health-related information-seeking and communication platforms for AYAs [26,29]. In addition, AYAs are reluctant to seek traditional forms of psychotherapy due to social stigma and discomfort in discussing personal problems and prefer digital interventions [24-26,30].

Despite the promise of mHealth interventions and the appeal to AYAs in particular, psychosocial mHealth interventions focused on improving QoL and psychosocial outcomes have not been evaluated or implemented among AYA oncology patients. This paper describes the protocol of an ongoing pilot RCT of a digitized version of PRISM deployed through a smartphone app (mobile app Promoting Resilience in Stress Management [mPRISM]).

## Methods

### Study Aims

The primary aim of this study is to evaluate the feasibility and acceptability of a self-guided mHealth resilience intervention (mPRISM) for AYAs with cancer. mPRISM content is based on stress and coping theory, resilience theory, and evidence-based psychosocial interventions. We hypothesize that mPRISM will be feasible as measured by ≥60% enrollment and ≥70% retention of participants to complete the study; and feasible, acceptable, and appropriate as measured by 3 brief well-established implementation measures (feasibility of intervention measure [FIM], acceptability of intervention measure [AIM], and intervention appropriateness measure [IAM] scores ≥4/5) [31]. Exploratory aims are to (1) examine preliminary efficacy assessed by validated patient-reported outcome measures at posttreatment and 3-month follow-up and (2) summarize digital usage metrics and engagement patterns under naturalistic conditions to inform future study design and to prepare participant instructions on how to use the app.

### Trial Design

This is a parallel, 2-arm, pilot RCT (Figure 1) [32]. Participants (N=80) with cancer will be enrolled and randomized to usual care (UC) or UC plus mPRISM at a single site. Using a waitlist design, mPRISM will be provided to the UC arm at a 3-month follow-up. Participant randomization to the study arm will occur after the completion of baseline surveys and in a 1:1 allocation ratio. As a waitlist design is being used, it is not possible to blind participants to the intervention condition [33]. Study outcomes, however, are completed independently by AYA participants to minimize bias.

**Figure 1 figure1:**
[figure not shown]
Schedule of all study activities. mPRISM: mobile app Promoting Resilience in Stress Management. T: timepoint.

### Participants

AYAs are eligible if they are (1) 12-25 years old; (2) within 12 months of diagnosis of new cancer; (3) receiving chemotherapy or radiation therapy at Seattle Children’s Hospital; (4) speak, read, or write English; and (5) have no cognitive limitations that would make participation difficult. We will provide iPads (Apple Inc) for the duration of the study for those who do not own a device.

Exclusion criteria include patient refusal to participate or parental refusal to participate for patients <18 years of age, patients who received a diagnosis of malignancy >12 months ago, patients with relapsed or refractory cancer, patients who have not received any chemotherapy or radiation therapy as part of their cancer treatment, cognitively or physically unable to participate, and previous participation in other PRISM-based studies. Clinical research coordinators will identify potential participants and prescreen through clinic rosters and electronic medical records. Recruitment by clinical research coordinators will occur remotely by phone, video, or SMS text messaging (ie, Zoom [Qumu Corp], Microsoft Teams, Webex [Cisco Systems], Skype [Microsoft Corp], email, SMS text messaging, and MyChart message [Epic Systems]).

### Intervention Conditions

#### UC

UC consists of standard nondirected supportive care provided for all patients including an assigned social worker who provides ad hoc services (mental health, financial, and housing support) at the request of the patient or family or medical team throughout cancer treatment. The AYA or their medical team can request referrals to psychology, psychiatry, pain medicine, child life, chaplaincy, palliative care, and art or music therapy.

#### Usual Care Plus mPRISM

In addition to UC, participants will receive access to mPRISM. PRISM is a brief, evidence-based resilience coaching intervention consisting of 4 scripted sessions delivered 1:1 by layperson coaches with high fidelity [11,14]. Sessions cover 4 core skills that are stress management (deep breathing, relaxation, and mindfulness techniques), goal setting (setting goals that are specific, measurable, actionable, and realistic, and planning around potential obstacles and barriers), cognitive reframing (identifying, challenging, and reframing negative thoughts), and meaning-making (identifying benefits, purpose, and meaning from cancer experience). Content from the in-person PRISM intervention was adapted to a mobile app (mPRISM), retaining core skills of the PRISM program (stress management, goal setting, cognitive reframing, and meaning-making [Figure 2]). Like the in-person PRISM program, mPRISM was co-designed with AYAs and with multiple iterations of stakeholder feedback. mPRISM contains tutorials showcasing audio-visual skills, dynamic skills practice opportunities, tracking systems of self-logged stress and resilience meters, a photo journal to review practiced skills, app notification reminders, and media links to other resources. AYAs randomized to mPRISM will receive a unique download code for the app. AYAs randomized to UC will receive a download code for the app after completion of their 3-month follow-up surveys. Once they receive access to mPRISM, all participants are instructed to use the app for 8 weeks.

**Figure 2 figure2:**
[figure not shown]
Selected examples of skills and practice materials on the mobile app version of Promoting Resilience in Stress Management. PRISM: Promoting Resilience in Stress Management.

#### Measures

Enrolled AYA participants will complete surveys at baseline before randomization, posttreatment (at 8 weeks), and 3-month follow-up (at 20 weeks). All surveys will be completed electronically by REDCap (Research Electronic Data Capture; Vanderbilt University) SMS text messaging or email survey invitation [34,35]. Survey responses will be scored based on measure scoring guidelines from the measure developers. In a waitlist design, the UC arm will receive mPRISM upon completion of the 3-month follow-up surveys to increase retention and optimize the use of the full sample size for analysis. This second wave of data collection for UC will include 2 additional measurement points at immediate posttreatment and 3 months later. Measure batteries at each timepoint take approximately 15-25 minutes to complete.

#### Data Storage

Data will be stored within a REDCap database on a secure, internal, HIPAA (Health Insurance Portability and Accountability Act)-compliant, password-protected Seattle Children’s server. Electronic consent will be stored in the same password-protected, secure database using the REDCap eConsent framework that securely collects, stores, and archives electronic consent information [34,35]. All electronic access to REDCap is encrypted.

#### Primary Outcomes: Feasibility, Acceptability, and Appropriateness

Feasibility is defined as ≥60% enrollment and ≥70% retention who complete the study. The FIM, AIM, and IAM are well-validated 4-item implementation science measures with strong reliability and validity [31]. Measures query perceptions of the feasibility, acceptability, and appropriateness of adopting an evidence-based practice. Items are rated on a 5-point Likert scale from “completely disagree” to “completely agree,” and total scores range from 1 to 5. Higher scores indicate greater acceptability, appropriateness, and feasibility, respectively. These 3 measures have been used independently and in conjunction. Feasibility, acceptability, and appropriateness cut-off scores are defined as measure scores ≥4 (on a 5-point scale).

#### Secondary and Exploratory Outcomes

##### Usability

The System Usability Scale (SUS) is a well-validated 10-item scale to evaluate the perceived usability of digital interventions with strong reliability and adequate validity [36]. Items are rated on a 5-point Likert scale for a total score ranging from 0 to 100, and scores ≥70 constitute adequate usability.

##### Health-Related Quality of Life

The PedsQL (Pediatric Quality of Life Inventory) 4.0 Generic and 3.0 Cancer Module include 50 items evaluating the HRQoL of AYAs with cancer and have strong reliability and validity [37]. Queries assess physical, emotional, social, and school well-being, plus cancer-related pain and hurt, nausea, procedural anxiety, treatment anxiety, worry, cognitive problems, perceived physical appearance, and communication. Items are rated on a 5-point Likert scale, and we will use the total scale score. Scores are linearly transformed to a 0 to 100 scale, with higher scores indicating better HRQoL.

##### Resilience

The Connor-Davidson Resilience Scale (CD-RISC) is a well-validated and widely used 10-item instrument to measure inherent resiliency that has demonstrated strong reliability and validity [38]. Questions revolve around personal problem-solving and approaches to adversity. Items are rated on a 5-point Likert scale; scores range from 0 to 40, and higher scores indicate higher resilience.

##### Distress

The Kessler Psychological Distress Scale (K6) is a 6-item scale that measures the level of psychological distress and has strong reliability and validity [39]. The instrument strongly discriminates between community cases and noncases of the *DSM-5* (*Diagnostic and Statistical Manual of Mental Disorders* [Fifth Edition]) psychiatric disorders such as serious emotional distress or serious mental illness. Items are rated on a 5-point Likert scale, scores range from 0 to 24, and higher scores indicate higher distress.

##### Anxiety and Depression

The Hospital Anxiety and Depression Scale (HADS) is a 7-item scale that assesses symptoms of anxiety and depression, respectively, in patients with serious illness [40]. It has been validated in AYAs with chronic illness and cancer survivors and has strong reliability and validity [41,42]. Items are scored 0-3 (subscale range 0-21), with scores ≥8 categorized as borderline abnormal, and ≥11 categorized as abnormal.

##### Digital Usage Metrics

Individual backend user data for mPRISM are collected in real time using Mixpanel, an event analytics service that tracks user engagement with mobile apps [43].

### Data Analysis

#### Power

The role of rigorous pilot studies such as this study is designed to determine feasibility [44,45]. Although not powered for efficacy, we will examine preliminary efficacy data for meaningful trends in terms of clinical significance with minimal clinically important difference (MCID) defined as half the SD for outcomes [46].

#### Primary Outcomes

Outcome domains will be assessed with Proctor’s framework [47] to determine implementation success (Table 1). Penetration will be assessed by clinic recruitment rates with ≥60% enrollment considered feasible. Uptake will be assessed through retention rates with ≥70% of participants completing the study considered feasible. We will apply top-box scoring [48] for the implementation measures, which is widely used in satisfaction research. Acceptability, appropriateness, and feasibility will be considered high if corresponding top-box scores are 80%.

**Table 1 table1:** Proctor’s domains assessed in data analysis plan.

Domain	Data analysis plan
Penetration	Recruitment rate
Uptake	Retention rate
Feasibility, acceptability, and appropriateness	Top-box scoring of validated implementation measures
Patient outcomes	Regression models of validated function and symptomatology measures

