### Ethical Considerations

All procedures are approved by the Seattle Children’s Hospital Institutional Review Board (STUDY00004006). The trial is registered at ClinicalTrials.gov (NCT05842902). All participants will provide informed consent (18-25 years old) or assent with parental consent (12-17 years old). Study participation is completely voluntary and participants are allowed to opt out of the study at any time. Privacy and confidentiality protections will be in accordance with institutional ethical guidelines. Study data are collected on secure, internal, HIPAA-compliant REDCap servers only accessible to the study team [34,35]. The collection of identifiable information is limited to that required to contact participants for study procedures and to report on sample demographics. Participants consented to use of data for study publications and no individually identifiable information will be reported in study publications. Participants will be compensated US $25 in electronic gift cards for completing each survey.

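### Uptake is scored by pooled study retention, which requires no app use and includes a usual-care arm without the app until after the week-20 surveys

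*Protocol article*

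**What the plan says.** In the protocol article, Data Analysis, Primary Outcomes, the outcome domains are taken from Proctor's framework and are meant to establish whether implementation succeeded. For one of these domains the text reads: "Uptake will be assessed through retention rates with ≥70% of participants completing the study considered feasible". Table 1 gives the same pairing, with retention rate as the only measure of Uptake.

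The abstract defines the quantity as "≥70% retention (ie, percentage of participants who completed the study", and Study Aims states the hypothesis as "≥60% enrollment and ≥70% retention of participants to complete the study". Neither place mentions app use or limits the denominator to one arm.

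On the design, Trial Design says: "Participants (N=80) with cancer will be enrolled and randomized to usual care (UC) or UC plus mPRISM at a single site", allocated "in a 1:1 allocation ratio". Under Usual Care Plus mPRISM, the UC arm gets its download code only once the 3-month follow-up surveys are done. Measures places those surveys at week 20 and gives UC two further measurement points after that.

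On app use, Digital Usage Metrics says: "Individual backend user data for mPRISM are collected in real time using Mixpanel". Under Data Analysis, Secondary and Exploratory Outcomes, these data are only described and graphed, with no threshold and no link to the Uptake domain.

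On surveys, Measures has them sent through REDCap, separately from the app, and Ethical Considerations adds: "Participants will be compensated US $25 in electronic gift cards for completing each survey".

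**The concern.** Uptake of a self-guided app concerns whether people who are given it start to use it. Retention concerns whether people stay in the trial and complete its assessments. The plan's own arrangements separate the two. The surveys arrive by another route, are paid one by one, and are also completed by participants who do not yet have the app. Measures gives better retention as one reason for the waitlist, so a design device raises the quantity that is then scored as uptake. Limitations names attrition and low adherence as distinct risks, but only retention carries a success criterion.

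A participant who never activates mPRISM but completes the study counts towards Uptake. A regular user who drops out of the surveys counts against it. The pilot is meant to inform a larger multisite trial. A statement that uptake was achieved would go into that planning although app use played no part in it.

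**Working it through.** **Inputs**
- Total sample 80, allocated 1:1 (Trial Design), so 80 / 2 = 40 per arm.
- Criterion: at least 70% completing (Primary Outcomes; Table 1 pairs it with Uptake).
- UC app access: after the 3-month follow-up surveys (Usual Care Plus mPRISM), that is, 8 + 12 = 20 weeks (Measures).
- Retention by arm: not given. The values below are assumptions, shown over a range.

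The article gives no sample-size or power calculation to reproduce. The only stated figure is the 70% threshold.

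**Step 1. Completers needed.** 0.70 × 80 = 56. UC supplies 40 / 80 = 50% of the denominator.

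**Step 2. How few mPRISM completers are enough.** mPRISM completers needed = 56 − UC completers.

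| UC retention (assumed) | UC completers | mPRISM completers needed | As % of 40 |
|---|---|---|---|
| 100% | 40 | 16 | 40% |
| 95% | 38 | 18 | 45% |
| 90% | 36 | 20 | 50% |
| 85% | 34 | 22 | 55% |
| 80% | 32 | 24 | 60% |
| 70% | 28 | 28 | 70% |

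**Step 3. Chance that the pooled rule passes with low mPRISM retention.** Completers are the sum of two independent binomials with n = 40 each; the rule passes at 56 or more.

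| True UC retention (assumed) | True mPRISM retention (assumed) | P(at least 56 of 80) |
|---|---|---|
| 90% | 60% | 0.89 |
| 90% | 55% | 0.75 |
| 90% | 50% | 0.56 |
| 85% | 60% | 0.75 |
| 85% | 55% | 0.56 |
| 85% | 50% | 0.35 |

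**Step 4. Where app use enters.** It does not enter steps 1 to 3. The article does not say which assessment marks completion, so both readings are needed:
- *Completion at week 20.* UC completers count towards Uptake before they have had access to the app.
- *UC completion includes the second wave.* UC completers have been issued a code by then, but nothing requires them to have activated it.

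On either reading, for either arm, the result is the same whether or not anyone opened the app.

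**Step 5. How far retention and use could differ (illustration).** Take 28 completers in the mPRISM arm and assume that one third of them never opened the app. Users among completers = 28 × 2/3 = 18.7. The 12 non-completers may or may not have used it:
- none did: 18.7 / 40 = 47%;
- all did: (18.7 + 12) / 40 = 77%.

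The one-third rate is an assumption without support in the article. The example shows only that 70% retention in the arm does not determine uptake.

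**The case against.** The strongest reply is that this is largely a matter of labelling. The abstract, Study Aims and the description of the primary outcomes all call 70% retention a feasibility criterion, and the word uptake appears only in the sentence quoted and in one row of Table 1. Relabelling would leave the hypothesis, the threshold and its pass or fail result unchanged. This stands as far as it goes: retention of at least 70% is a sound criterion for trial feasibility. It does not rescue its use as the sole measure of a separately named implementation domain.

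A second reply is that leaving usage without a threshold is deliberate. Study Aims makes usage exploratory, to be observed under naturalistic conditions, and the descriptive summaries can reveal low or absent use. That is also fair. But the article itself fixes the pairing of Uptake with retention, so the choice is not one left to an analysis plan, and the summaries as planned cannot change the Uptake result.

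Two stronger readings are tempting, and the article does not support them. A reader might infer that the whole primary assessment could succeed with negligible app use. The FIM, AIM and IAM ratings are also primary outcomes, with a cut-off of 4 out of 5 and an 80% top-box bar, and they ask about the intervention. They record perceptions, not use, so they do not fill the gap. But high ratings from people who hardly opened the app are only a logical possibility, and nothing in the article makes them likely. A reader might also take the 47% in step 5 as the true uptake hidden behind a passed criterion. That figure counts every non-completer as a non-user; the same assumption allows anything up to 77%.

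**Conclusion.** The point holds for the Uptake domain. Retention pooled over both arms does not measure uptake of mPRISM, and the criterion can be declared met whatever the app use. Even as a measure of staying in the trial, pooling lets the mPRISM arm fall to 40% if every UC participant completes, or to 50% at an assumed UC retention of 90%.

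The first of these figures rests only on the stated sample size, allocation and threshold. The others depend on assumed retention by arm. Reading completion of the study as completion of its surveys is an inference, since these are the only assessments that participants are described as completing. The finding does not touch retention as a trial-feasibility criterion, the enrollment criterion or the implementation ratings.

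**What to change.** - Keep retention of at least 70% as a criterion of trial (data-collection) feasibility, under that name, and report it by arm as well as pooled. State which assessment marks completion in each arm.
- In Primary Outcomes and Table 1, define Uptake from the Mixpanel records as the proportion of participants issued a download code who activate and use the app within the 8-week period. Make the mPRISM arm (40 participants) the main group and show UC after crossover separately.
- Fix what counts as use, and any threshold, before analysis. The article supports no particular cut, so this is for the sponsor to choose. If 70% were carried over, for illustration only, the mPRISM arm would need 0.70 × 40 = 28 users.

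The cost is a change of wording and one extra tabulation of data already being collected. Data collection is expected to run to 2027, which leaves time to specify this in advance. The downside is that the uptake figure may be less favourable than the retention figure.
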